### Randomization and Blinding

A block randomization scheme with a block size of 4 will allocate participants to 1 of the 2 intervention sequences (VR-PAT followed by control or control followed by VR-PAT) at a 1:1 ratio without stratification. We chose a block randomization strategy to avoid imbalances in allocation to the intervention at the first visit in case we were unable to recruit our planned sample. The randomization scheme was developed and uploaded to a study-specific REDCap (Research Electronic Data Capture; Vanderbilt University) project by the project manager. Study participants are randomized into intervention sequences after signing consent and completing the baseline survey. Research recruiters and participants are not aware of the intervention assignment until the participant is randomized in REDCap.

We cannot blind the participants or the clinical team to the assigned intervention since the headset will either be turned on or off. The researcher who randomized the participant and observed the laser procedure will not be blinded, but a second researcher, who is blinded to the intervention group, will collect pain ratings and anxiety post procedure. The second researcher will wait in a different room during randomization and the laser procedure, and the first researcher will remind the participant at the end of the laser procedure to keep their group a secret until they are asked. The study biostatistician will also be blinded to the intervention group while performing analyses on the primary outcome. The data will be blinded by removing labels such as “VR” and “Control” and replacing them with unidentifiable letters (eg, “A” and “B”). The biostatistician will need to be unblinded for secondary outcomes, as only participants in the intervention group will answer the VR experience questions.

The blinded researcher will need to be unblinded after pain and anxiety ratings are obtained, as those in the control environment will not be able to answer the VR experience questions. The researcher will become unblinded by asking participants whether they played the game. The biostatistician will also be unblinded for full analyses by being provided with the full dataset, including complete data labels and VR questions. This unblinding will take place after the primary outcome analysis has been completed.

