### Sample Size

Since this is a pilot study, the focus of the statistical analysis will be on estimating the effect sizes of VR-PAT and their 95% CI, as well as the variances of the outcome measures. These findings will facilitate sample size calculations and study power estimates for future larger-scale randomized trials. We decided on a sample of 40 participants and 2 research visits based on the grant budget and the patient volume for the 1 dermatologist collaborating on this study.

Across acute pain studies, clinically meaningful improvements are generally larger than a 1-point change on the NRS 0‐10, with systematic review evidence suggesting minimum clinically important differences of approximately 13% to 36% reduction, with a median of 23% (IQR 18%-36%), corresponding to roughly 1.4‐2.3 points on the NRS [38,39].

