### Data Analysis

To achieve aim 1, composite scores will be calculated for each laser procedure, encompassing the pain score, pain medication use during the procedure, and whether rescue medication was used. The rationale for choosing the composite score as the outcome is that prior researchers have shown a significantly high positive relationship between pain medication use and self-reported pain scores [40]. From a clinical perspective, pain scores alone are influenced by the patients’ actual opioid use and may not fully reflect the treatment benefit of VR [41]. The composite score approach, therefore, provides a single, patient-centered outcome that represents overall analgesic benefit, aligning with the goal of achieving adequate pain control while minimizing opioid exposure. In our analysis, we will apply the rank-based approach by Dai et al [40] to assign weights to pain and medication use, reflecting their complementary clinical importance as measures of pain reduction [41]. In the primary analysis, the composite scores from the laser procedure with VR will be compared to those from the procedure with standard care (ie, control) using paired 1-tailed *t* tests or the Wilcoxon signed rank tests (depending on the distribution of the composite scores) due to the cross-over design. The clinical effect size will be the mean difference (if paired *t* tests are used) or median difference (if Wilcoxon signed rank tests are used) in the composite score between VR and control procedures. The SD of the difference will also be calculated.

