Linear mixed-effects models with participant-specific random intercepts will be fit on the composite scores to evaluate any modification of the effects of VR on pain by sex, age, and anxiety, with adjustment for baseline covariates and potential carryover effects of VR from the first to the second procedure. The following covariates will be included in the regression models: study group (VR vs control), period (second vs first procedure), study group by period interaction (test for carryover effect), age, age by study group interaction, sex, sex by study group interaction, procedural anxiety, procedural anxiety by study group interaction, race, ethnicity, State-Trait Anxiety Inventory for Children, 6-item State-Trait Anxiety Inventory, and average mYPAS scores between T0 and T1. We will include each of the 3 interaction terms in a separate regression model. Due to the limited sample size, testing the interaction may not be feasible. The study will then run the main linear models without interaction terms. The results will provide us with preliminary data to estimate the future study sample size and power. In case a significant carryover effect is detected, we will use only data from the first procedure to evaluate the VR effect using 2-sample *t* test or Wilcoxon rank sum tests (depending on the distribution of the composite scores).

All statistical analyses will follow the intention-to-treat principle, wherein participants will be analyzed according to their assigned study groups, regardless of compliance status or group switching during the study.

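### The carryover pretest that moves the VR comparison to first-visit data moderately inflates the false-positive rate, and gives an unreliable estimate whenever it fires

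*Protocol article*

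**What the plan says.** All points below are from the protocol article.

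- **Primary analysis (Data Analysis).** The composite pain score at the VR procedure is compared with that at the procedure "with standard care (ie, control) using paired 1-tailed" t tests, or by signed rank tests. The effect size is the paired mean or median difference, and the SD of the difference is also to be calculated.
- **Carryover (Data Analysis).** The mixed models for the composite score list a "study group by period interaction (test for carryover effect" among their terms. The consequence of a significant result is fixed: "In case a significant carryover effect is detected, we will use only data from the first procedure to evaluate the VR effect". The replacement is a two-sample t or rank sum test, "depending on the distribution of the composite scores". No level is given for the carryover test, and neither a sidedness nor an adjustment is given for the replacement test.
- **Caveat (Data Analysis).** Interaction testing may prove infeasible at this sample size, in which case models without interaction terms are run. No criterion is stated.
- **Design.** Allocation to the two sequences is "at a 1:1 ratio without stratification". Visits are about 6 to 8 weeks apart (Trial Design). The size was set as follows: "We decided on a sample of 40 participants and 2 research visits based on the grant budget" and on patient volume (Sample Size). In all, 44 participants completed the first visit and 40 completed both (Results).
- **Purpose (Sample Size).** The focus is on "estimating the effect sizes of VR-PAT and their 95% CI", together with variances, for planning a larger trial.

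**The concern.** The group-by-period term in this design is a between-participant comparison, and it shares the first-visit data with the analysis that it triggers. A chance imbalance between the sequences at the first visit makes the pretest more likely to be significant. It is then the imbalanced first-visit data that supply the VR estimate. Nothing in the plan corrects for this.

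Two things are at stake. The two-stage procedure does not hold its nominal error rate. In a trial that switches, the effect size and confidence interval would also be poor inputs for planning the next study, although those quantities are what this pilot is meant to deliver. The switch further sets aside the within-participant comparison that the Discussion names as the design's strength.

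**Working it through.** The plan gives no alpha, power or SD calculation, so there is no figure to reproduce. What follows is a check of the rule's behaviour.

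**Inputs.** From the article: 40 completers, 1:1 to two sequences, a paired one-tailed primary test, and a first-visit two-sample test after a significant carryover test. Assumed, because not stated: exactly 20 per sequence, a nominal 5% efficacy test, a two-sided pretest at 5% or 10%, normal scores with SD 1, within-person correlation ρ of 0.3 to 0.7, no covariate adjustment and no period effect.

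**1. Overlap of pretest and fallback.** The pretest compares Y1+Y2 between sequences; the fallback compares Y1. The covariance of Y1 with Y1+Y2 is 1+ρ, and the variance of Y1+Y2 is 2(1+ρ). The correlation of the two contrasts is therefore (1+ρ)/√(2(1+ρ)) = √((1+ρ)/2), which is 0.81, 0.87 and 0.92 at ρ = 0.3, 0.5 and 0.7.

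**2. Power of the pretest.** For a carryover of 0.5 SD at ρ = 0.5, the standard error of the difference in totals is √(2(1+ρ) × 2/20) = √0.30 = 0.548, and 0.5/0.548 = 0.91. Against critical values of 1.96 (5%) and 1.645 (10%), power is about 15% and 23%. By simulation at 5%, with a true effect of 0.5 SD and carryover equal to it, the pretest is significant in 13-16% of trials across ρ = 0.3-0.7.

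**3. Overall one-sided false-positive rate** (simulation, no VR effect and no carryover, nominal 5%):

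| Pretest level | ρ = 0.3 | ρ = 0.5 | ρ = 0.7 |
|---|---|---|---|
| 5% | 6.3% | 6.6% | 6.9% |
| 10% | 7.0% | 7.3% | 7.7% |
| No pretest, always paired | 4.9-5.1% | 4.9-5.1% | 4.9-5.1% |

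Repeat runs differ by about 0.1 to 0.2 points, so the 10% row is best read as 7.0-7.8%. Using all 44 first-visit participants (22 v 22) with a 5% pretest still gives 6.2-6.7%.

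**4. Trials in which the switch fires** (about 5% or 10% of trials without carryover):

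- The first-visit test rejects a true null in about 32-43% of them after a 5% pretest and 25-33% after a 10% pretest (one-sided).
- The nominal 95% CI covers the truth in about 36-57% (5% pretest; another run gave 38-55%) or 57-69% (10% pretest).
- At ρ = 0.5 and a 5% pretest, the first-visit estimate has an SD of about 0.65 against 0.32 unconditionally. Its mean is about 0 when the true effect is 0, and about 0.50 when it is 0.5.

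**5. Precision after a switch.** The first-visit standard error is √(2/20) = 0.316. The paired standard error is √(2(1−ρ)/40) = 0.187, 0.158 and 0.122. The ratio √(2/(1−ρ)) is 1.69, 2.0 and 2.58. At a true effect of 0.5 SD, one-sided power is 84%, 93% and 99% for the paired test, and about 46% for first-visit data alone.

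**The case against.** **Small overall.** The inflation is from 5% to 6-7% with a 5% pretest. Without carryover the average power loss is also small: at effects of 0.4 to 0.6 SD it runs from 67.9 − 66.9 = 1.0 point (0.4 SD, ρ = 0.3) to 99.9 − 97.4 = 2.5 points (0.6 SD, ρ = 0.7). For a pilot focused on estimation this does not invalidate the study. That stands and limits the severity.

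**The planned pretest is covariate-adjusted and the composite is rank-based.** If covariates explained half of the between-person variance (an assumption), the one-sided rate would be about 5.9-6.0%. That also stands: the direction persists, but the size is not established for the exact plan.

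**The rule guards against real carryover.** In part it does. With carryover equal to a 0.5 SD effect, the paired estimate is halved to 0.25 SD. At ρ = 0.5 the two-stage rule then rejects in 52% of trials against 44% for the paired test. But the pretest misses that carryover in about 85% of trials, so the protection is slight.

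**Stronger readings that the article does not support:**

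- A reader might infer that the triggered estimate is biased in one direction. Without carryover it is centred on the truth and only overdispersed.
- A reader might infer that the crossover's precision is lost outright, or that planning figures would come only from about 20 v 20. The paired comparison is the primary analysis, the paired difference and its SD are specified separately, and nothing says that they go unreported after a switch.
- A reader might infer that the mixed model's VR coefficient is necessarily a first-visit effect. That depends on the reference coding, applies only while group-by-period is in the model, and overlooks the provision for models without interactions. Because that provision has no criterion, however, it leaves open whether the pretest is run at all.

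**Conclusion.** The concern holds as a should-fix point. The article commits to an unadjusted carryover pretest that changes which data estimate the VR effect. Under the assumptions listed, the one-sided false-positive rate rises from 5% to about 6.3-6.9% (5% pretest) or 7.0-7.8% (10% pretest), and somewhat less if the covariates are informative. The damage is concentrated in the roughly 5-10% of no-carryover trials that switch, where the interval is far from its nominal coverage and the standard error is 1.7-2.6 times larger. The excess over 5% appeared at every correlation tried; its exact size depends on an alpha, a pretest level, a correlation and a distribution that the article does not give.

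**What to change.** Before unblinding:

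1. Delete the sentence that switches to first-procedure data.
2. State that the within-participant, period-adjusted estimate from both visits is the primary result whatever the carryover test shows. Take the VR estimate from a model without group-by-period, in line with the article's own provision for models without interaction terms.
3. Always report the first-visit contrast and the carryover estimate, each with its CI, as sensitivity analyses that trigger nothing.
4. State absence of carryover as a design assumption, supported but not proven by the 6 to 8 week gap. The article's own background says that procedural distress can affect later treatments, so a learned response may outlast the interval.

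The cost is wording only and no new data. Data collection is complete and analysis is due to finish in June 2026. Under the blinding plan the biostatistician stays blinded until the primary analysis is done, so a change made before then need not look data-driven.

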### Ethical Considerations

The NCH IRB approved this study (STUDY00002880) initially on October 17, 2022, and protocol version 6 was approved on April 1, 2025. Important protocol modifications have been communicated to study personnel by the project manager and will continue to be communicated. Written, informed consent to participate was obtained from one parent or legal guardian of all participants younger than 18 years, and from the participant if they are aged 18 years or older. Additionally, written assent was obtained from participants aged 9 years and older, as per the NCH IRB policy for written assent. This trial has been registered on ClinicalTrials.gov (NCT05645224), where detailed information about the study protocol, inclusion and exclusion criteria, interventions, outcomes, and ethical approval can be found. The trial registration process was completed before the enrollment of the first participant.

## Results

This study was funded by an intramural grant from the Clinical and Translational Science Institute at NCH (grant: IFPAWRI012023) in January 2023. Enrollment started in January 2023, and data collection was completed in November 2025. The flow of participants can be seen in Figure 1. A total of 44 patients were recruited and completed the first visit, with 40 participants completing both visits. The sample was balanced, with 40 patients using the VR intervention and 40 patients participating in the control group. Reasons for not completing both visits included discontinuing laser treatment (n=3) and a lack of interest in playing the VR game (n=1). Among those who completed both visits, the age range of the sample was 6 to 21 years at recruitment, and 55% (n=22) were female. Data analysis is expected to be finished in June 2026, with a paper to follow. Future results will be disseminated through publications in peer-reviewed journals and abstracts submitted to conferences in relevant disciplines.

**Figure 1. F1:**
[figure not shown]
Flow diagram for a crossover, randomized clinical trial investigating the use of virtual reality during dermatologic laser procedures.

## Discussion

Our VR-PAT protocols have been successfully implemented in our prior and ongoing studies, and we believe this protocol will be successful in a new setting. Prior VR research has been shown to significantly reduce self-reported pain [21-23], anxiety [10,24], and time spent thinking about pain [10,23] during painful pediatric procedures. Similar findings are anticipated in this outpatient laser study. The authors also anticipate very few reports of simulator sickness, as this study uses the same VR-PAT that has been previously used during pediatric burn dressing changes [29,31], in the emergency department [43], and during pin-pulling procedures [43]. We expect this intervention to be feasible to implement, with nurses reporting a high degree of helpfulness and ease of use, similar to our previous work [29].

The strength of this study is that laser procedures are unique clinically, in that the pain stimulus is the same for each procedure. This allows the use of a crossover study design and within-participant comparisons. Our prior VR research has been conducted during burn dressing changes, which are subject to healing over time, making each dressing change a different pain experience. Another strength of this study is providing pain and anxiety distraction during an outpatient procedure, which has historically been difficult to achieve. To maintain laser safety, shiny surfaces must be limited to avoid a reflection of the laser beam, and ocular safety requires glasses that filter the light waves and can alter the colors that patients can see. Since our VR headset passed laser safety testing, it can be a valuable tool for this patient population. Finally, we have found that the proportion of participants recruited is high among those we have approached and retention has been high among those patients who returned to the clinic for their second laser visit. Part of the retention success can be attributed to the study’s buy-in from the clinic nurses. They have helped to keep excitement high among participants by talking to them about the VR game during the laser procedures, and they have even developed an anonymized scoreboard for participants to keep track of their scores. The nurses also keep the VR headset charged and clean to ensure the study implementation runs smoothly.

This study is subject to some known limitations. First, all the participants come from the same hospital, and all the laser procedures are performed by the same physician, which limits our ability to generalize the findings. Second, since complete blinding was not possible due to the nature of the intervention, there is a chance of expectation bias among participants and clinicians. The research team attempted to manage participants’ expectations at recruitment and prior to each visit by explaining the research nature of the VR. A choice was also made not to measure participants’ expectations for the VR because we felt that this would prompt a reflection on their expectations and peak excitement. The third limitation is in evaluating the possible sample size. There has been more loss to follow-up than anticipated due to patients not following up clinically. This limits the ability to retain them in this research study. The proportion of eligible participants who were recruited is also lower than expected. This is largely related to many screened patients not ultimately scheduling a laser procedure. This will be a consideration for future studies in determining the number of physicians and/or sites needed to complete a powered study.

The future research direction, following the successful completion of this study, depends on the results but could include a fully powered efficacy study and, eventually, a multisite implementation study. In designing future implementation and dissemination work, sustainability will be a priority. This will include evaluating insurance reimbursement to cover the cost of owning and using this VR. We would follow in the footsteps of companies like AppliedVR, which was the first VR to obtain US Food and Drug Administration–authorization and established a unique Healthcare Common Procedure Coding System Level II code [44].

In conclusion, patients needing outpatient laser therapy have unique needs for pain and anxiety management, particularly in the context of ocular protection from laser damage. VR is a promising digital technology that can improve the experience of patients requiring dermatologic laser therapy. We anticipate that findings from this innovative randomized clinical trial will provide early evidence on the efficacy of VR-PAT in reducing self-reported pain and anxiety during outpatient laser procedures.
